#### Secondary outcomes

The secondary outcomes are HRQoL and progression-free survival (PFS). For HRQoL, we will use the Constant–Murley scale to evaluate patients’ shoulder function, with follow-up at 7 days, 21 days, 3 months, 6 months, 1 year, 2 years and 3 years after surgery.

There are many reasons for setting OS as the primary outcome. First, it is widely used as a reliable indicator for evaluating the prognosis of tumors. It is reported that the 3-year OS rate in an IIb dissection group is about 80% [1], which includes disease-free survival and living with disease. Metastasis in level IIb is extremely low, and even if it happens it is nonlethal and can be instantaneously controlled by surgery or radiotherapy. Theoretically, 3-year OS in the IIb retention group will resemble that in the dissection group. A summary of 38 RCTs [7, 23] reports no significant association between PFS duration and HRQoL. In addition, as PFS is not as reliable as OS and can also increase difficulties in follow-up, we did not use PFS as the primary outcome.

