#### Follow-up

Follow-up timepoints include immediately, 7 days, 1 month, 6 months, 1 year, 1.5 years, 2 years, 2.5 years and 3 years after surgery. Follow-up will include physical examination, enhanced CT/MRI, bilateral neck B-scan ultrasonography, Constant–Murley score and a safety observation. There will be different evaluations at different timepoints, but overall evaluation will be the same between the two groups. The number of patients who quit our trial for any reason during follow-up will be represented as *m*_3_, and the number of patients who will be included in our analysis will be represented as *n*_4_ (see Fig. 3 for details).

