#### Secondary outcomes

For HRQoL, we will use the Constant–Murley scale to evaluate shoulder function at each follow-up timepoint. In order to improve the reliability of shoulder function evaluation, two clinicians will be systematically trained on use of the scale.

For PFS, observations will start at time of randomization and end when events (see below) occurred. In the period of time from randomization (Fig. 3) to any primary recurrence, local metastasis, distant metastasis, and other life-threatening events or death will be defined as PFS.

If a patient has not returned to the clinic for more than 2 months after the follow-up timepoint, a telephone inquiry will be conducted.

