#### HRQoL

We will use a repeated analysis of variance (ANOVA) measure to analyze changes in Constant–Murley score between the two groups. It is reported that about 67% of patients have shoulder syndrome after neck dissection even if the accessory nerve is spared [26]. Currently, two methods might work to deal with the problem of shoulder dysfunction. The first is to restore the damaged nerve with such methods as intraoperative brief electrical stimulation of the spinal accessory nerve (BEST SPIN). However, this technique has little effect [27], and literature on the treatment of damaged accessory nerves is rare. The second is retention of level IIb during surgery to preserve the integrity of accessory nerve function and structure. By measuring changes in the action potential of the accessory nerve during surgery it was found that level IIb dissection can greatly damage the accessory nerve [6]. We will use the Constant–Murley scale [28] to assess shoulder function. Although the scale’s reliability in evaluating shoulder function has been questioned [29], it has been clinically applied for more than 30 years, and it can reflect both subjective indicators (such as pain or daily activity) and objective standards (such as the muscle mobility and power). Because of the tissue defect caused by primary resection, distant free or adjacent flaps are used to restore it. In order to ensure the flaps are alive, movement control after surgery is crucial. Patients with free flaps are clinically permitted to lift the upper body on the fifth day after surgery and can also sit up in bed. On the sixth day after surgery, mild activities such as walking are permitted. Therefore, the first timepoint for evaluating shoulder function will be the seventh day after surgery, and then there will be follow-up at 1 month, 6 months, 1 year, 2 years and 3 years.

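### Shoulder function is first scored on day 7, after the nerve injury, so the planned analysis of change has no pretreatment reference; add a preoperative score

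*Protocol article*

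**What the plan says.** Under Statistical methods, HRQoL, the Protocol article says: "We will use a repeated analysis of variance (ANOVA) measure to analyze changes in Constant–Murley score between the two groups". It does not say what change is measured from. The same paragraph argues from flap protection and restricted movement in the first postoperative days, and concludes: "Therefore, the first timepoint for evaluating shoulder function will be the seventh day after surgery". It continues: "then there will be follow-up at 1 month, 6 months, 1 year, 2 years and 3 years".

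The other sections also name only postoperative times:

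- Outcomes, Secondary outcomes: "with follow-up at 7 days, 21 days, 3 months, 6 months, 1 year, 2 years and 3 years after surgery".
- Participant timeline, Follow-up: "Follow-up timepoints include immediately, 7 days, 1 month, 6 months, 1 year, 1.5 years, 2 years, 2.5 years and 3 years after surgery".
- Data collection methods, Secondary outcomes: "we will use the Constant–Murley scale to evaluate shoulder function at each follow-up timepoint".

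The Background places the accessory-nerve injury in the operation itself, when the nerve is pulled during level IIb dissection. The HRQoL section likewise expects more nerve damage where IIb is dissected.

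**The concern.** An analysis of change needs a reference that treatment has not affected. Here the exposure that separates the arms is complete before the first score is taken, so day 7 carries part of the treatment effect. Change counted from day 7 measures recovery, and the arm that was hurt more has more to recover.

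The flap argument explains why no one is tested before day 7 after surgery. It gives no reason against testing before surgery.

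Survival is tested for non-inferiority with a 12% margin, so the reason to prefer retention is the expected shoulder benefit. The Constant–Murley score is the only shoulder or quality-of-life instrument the article names. A misread shoulder result would weaken the case the trial is meant to examine. A preoperative score cannot be recovered once the patient has been operated on.

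**Working it through.** The article gives no mean, standard deviation, effect size or power for the Constant–Murley score, so there is no stated figure to reproduce. Every score below is an assumption; only the arm size (about 260, from Sample size) and the visit times are the protocol's.

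**1. Direction of the contrast.** Let G7 be the gap in mean score (retention minus dissection) at day 7 and GL the gap at a later visit. With equal preoperative means, as randomisation gives in expectation:

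- arm difference in change from the preoperative score = GL
- arm difference in change from day 7 = GL − G7

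If retention is better at day 7 (G7 > 0) and dissection partly catches up (0 < GL < G7), the first is positive and the second negative.

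| G7 | GL | Change from preoperative | Change from day 7 |
|---|---|---|---|
| 5 | 2.5 | +2.5 | −2.5 |
| 10 | 5 | +5 | −5 |
| 10 | 10 | +10 | 0 |
| 15 | 7.5 | +7.5 | −7.5 |

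For G7 from 5 to 15 and a remaining share of the gap from 0 to 100%, the day-7 contrast runs from −15 to 0. The preoperative contrast runs from 0 to +15.

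**2. How often this would reach significance.** Assume SD 15, 260 per arm, within-patient correlation ρ of 0.5 or 0.7, and gaps at the six visits in the HRQoL section of 10, 9, 7.5, 6, 5 and 5. Retention is then better at every visit.

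- Change from day 7 to 1 year: difference 6 − 10 = −4. SE = √(2 × 2 × 15² × (1 − ρ)/260) = 1.316 at ρ = 0.5 and 1.019 at ρ = 0.7. The probability of a significant result favouring dissection is Φ(4/SE − 1.96) = 86% and 97%. A simulation of 1,000 trials gave 84% and 97%.
- Level at 1 year: difference +6, SE = √(2 × 15²/260) = 1.316, Φ(6/1.316 − 1.96) = 99.5% in favour of retention (simulated: about 99%).

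Other cases, simulated:

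- Day-7 gap of 5 shrinking to 2.5 (3 at 1 year): change from day 7 significantly favoured dissection in 35% (ρ = 0.5) and 52% (ρ = 0.7) of runs.
- Gap constant at 10: 2% to 3%, the chance rate.
- Between-group main effect of the repeated-measures ANOVA, which compares mean postoperative level: favoured retention in 88% to 100% of runs across all cases.

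The reversal therefore belongs to change from day 7 and to the group-by-time term, not to the comparison of levels.

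**3. Precision.** Adjusting a single-visit comparison for a baseline score correlated r with it leaves residual variance 1 − r²: 0.91 at r = 0.3, 0.75 at r = 0.5 and 0.51 at r = 0.7. At r = 0.5 this is worth 1/0.75 = 1.33, or a one-third larger sample for that comparison.

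**The case against.** Four arguments stand against the point.

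*The figures may show a baseline.* Figure 2 (visits and assessments) and Figure 3 (timeline) are not readable here, and a baseline score would normally appear there. The lists in the text are follow-up lists, and the day-7 sentence closes an argument about postoperative movement, so it may mean only the first postoperative assessment. This limits how firmly the absence can be stated. But the sentence as written calls day 7 the first evaluation, without qualification. If the figures list an earlier score, they contradict that sentence and it still needs rewording.

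*The plan never names day 7 as the reference.* This is true, and the exact contrast may be left to an analysis plan that is not shown. The reversal is therefore conditional. Even so, the plan says it will analyse changes, and day 7 is the earliest score that the readable text provides.

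*Randomisation protects the comparison of levels.* This stands in full. A reader might infer that without a preoperative score the shoulder comparison is biased, or that pre-existing shoulder limitation confounds it. The documents do not support that: with about 260 per arm, prior limitation is balanced in expectation. What is lost is precision and each patient's own reference. The article does not list return to baseline as an outcome.

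*The outcome is secondary and no shoulder power is claimed.* This also stands. The precision figure is a gain forgone, not a failed target, and overall survival is untouched.

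**Conclusion.** The point holds as a should-fix improvement. On the readable text, the plan analyses change in a score first taken after the injury it is meant to capture, and the reference for change is undefined. If change is taken from day 7, or read from the group-by-time term, and the dissection arm partly recovers, the sign can reverse. Under the assumed values in the working, a significant reversal occurs in roughly a third of trials to nearly all of them; with no catch-up it occurs only by chance. These sizes rest on assumed gaps, SD and correlations, since the article supplies none.

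A reader might go further and conclude that the planned ANOVA will favour the more damaged arm. The documents do not support this: day 7 is not named as baseline, and the ANOVA's between-group effect does not reverse. The certain losses are smaller: the precision of baseline adjustment, and any statement of how much function each patient lost or regained relative to before surgery.

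**What to change.** 1. Add one Constant–Murley assessment of the shoulder on the side or sides to be operated, before surgery and before allocation is revealed.
2. Reword the HRQoL section so that the preoperative score is the first assessment and day 7 the first postoperative one. Make Figures 2 and 3 agree.
3. Include the preoperative score as a covariate in the repeated-measures model.
4. Define the treatment effect as the between-arm difference in postoperative score at named visits. With the preoperative score as covariate, this equals the difference in change from that score. State that day 7 is never the reference.

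Naming the visits also requires reconciling the shoulder schedules: Secondary outcomes lists 21 days and 3 months, while the HRQoL section lists 1 month and neither of those.

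The cost is one extra administration of the scale per patient. The scale is already in use, two clinicians are to be trained on it, patients are already examined before surgery for eligibility, and enrolment had not started at this protocol version.

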#### Progression-free survival

We will use a two-sided log-rank test to check the difference in PFS between the two groups.

#### Others

In addition, we will use post-hoc subgroup analyses on the basis of histological factors that were known to have effects on survival, such as depth of invasion of the primary tumor.

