**Methods:**

We designed a parallel-group, randomized, non-inferiority trial that is supported by Shanghai Ninth People’s Hospital, Shanghai Jiao Tong University, School of Medicine, Shanghai, China. We will enroll 522 patients with early oral carcinoma who match the inclusion criteria, and compare differences in 3-year overall survival, progression–free survival (PFS) and HRQoL under different interventions (retention or dissection of level IIb). The primary endpoints will be tested by means of two-sided log-rank tests. Analysis of overall and progression-free survival will be performed in subgroups that were defined according to stratification factors with the use of univariate Cox analysis. In addition, we will use post-hoc subgroup analyses on the basis of histological factors that were known to have effects on survival, such as death of invasion of the primary tumor. To evaluate HRQoL, we will choose the Constant–Murley scale to measure shoulder function.

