### Sample size

In calculating the sample size, we assumed the 3-year OS rate in the IIb retention group will be about 78%, α = 0.05 (one-sided), power of 80% (β = 20), and that in the IIb dissection group will be 80% [1]. The noninferiority margin will be 12%, so the sample size as generated by PASS Sample Size Software 15.0 (NCSS LLC, Kaysville, Utah, USA) will be 261 for IIb retention and 260 for IIb dissection. To obtain a reasonable sample size and make sure the trial is instructive for clinical work, we combined the common opinions of oral and maxillofacial experts, and the statistician defined the noninferiority margin as 12% [24]. Although the value seems to be large, its role is to control the large sample size that would otherwise be unapproachable.

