### Stratification

OS can be affected by many factors, such as T stage (T1, T2), primary subsite (tongue, buccal mucosa, mouth floor, gingiva, posterior molar region or hard palate), and depth of invasion [25]. To balance the number of patients between groups and minimize the bias of the trial, we will use T stage and primary subsite for stratification.

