Our trial has some limitations. First, currently it is noteworthy that, for T1 N0 OSCC, many surgeons would actually not undertake a staging neck dissection, which seems in contrast to the study. However, according to the NCCN guidelines, the recommended treatment options for T1 and T2 are the same, being resection of primary (preferred) and/or ipsilateral (guided by tumor thickness) or bilateral (guided by location of primary) neck dissection or sentinel lymph node biopsy [19]. In order to clarify the relationship between the depth of invasion and occult metastasis, we will put the depth of invasion into the final analysis. Second, at present there are many auxiliary methods for cervical examination, such as B-scan ultrasound, enhanced CT/MRI, ^18^F-fluorodeoxyglucose positron emission tomography (PET)/CT, and CT, etc. In this trial, we will use B-scan ultrasound and enhanced CT/MRI to detect occult metastatic lymph nodes. However, the sensitivity of these examinations is not high. It has been reported that PET/CT offers a distinct advantage over other conventional imaging modalities because it provides functional insights into tumor biology and tissue metabolism, and thus PET/CT has a higher sensitivity and advantages for detecting cervical metastasis. However, PET/CT also has some limitations. The cost is relatively high and, besides, the main advantage of PET/CT applies to clinically node-positive OSCC, and PET/CT has a higher false negative rate for detecting nodal involvement in the setting of a cN0 neck. NCCN guidelines currently recommend PET/CT imaging for most stage III and IV OSCC [39]. Therefore, in our trial, PET/CT is not considered for detecting neck status.

In summary, this parallel-group, randomized, noninferiority controlled trial aims to assess whether IIb neck dissection should be performed in T1–T2 N0 OSCC and to also assess the effects of IIb neck dissection on OS and HRQoL. Although there are some limitations to this study, it is still worth conducting for the advantages it may have for patients.

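### Minor: the stated univariate Cox subgroup analyses do not test whether the effect of retaining level IIb differs by T stage or subsite, and the depth-of-invasion subgroup announced before enrolment is labelled post-hoc

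*Protocol article*

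**What the plan says.** Two separate subgroup plans appear in the protocol article.

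- **Stratification factors.** The Methods part of the abstract says that overall survival (OS) and progression-free survival (PFS) will be analysed in "subgroups that were defined according to stratification factors with the use of univariate Cox analysis". The Stratification section identifies the factors: "we will use T stage and primary subsite for stratification". It lists their levels: "such as T stage (T1, T2), primary subsite (tongue, buccal mucosa, mouth floor, gingiva, posterior molar region or hard palate". The Statistical methods section neither repeats nor changes the Cox statement.
- **Histological factors.** The abstract and the Others paragraph of Statistical methods both say "we will use post-hoc subgroup analyses on the basis of histological factors that were known to have effects on survival", with depth of invasion as the example. No model is named for this analysis.

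The Stratification section already lists depth of invasion among the factors that affect OS, although it is not used to stratify. The Trial status section says that enrolment had not begun when this version was written.

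**The concern.** **The method.** A univariate Cox model fitted within a subgroup has treatment as its only covariate. It estimates the hazard ratio of retention against dissection in that subgroup. It has no treatment-by-factor term, so it cannot show whether the hazard ratio in one subgroup differs from that in another. Comparing p-values across levels is not a substitute. A level can reach p<0.05 by chance, and a level with few deaths can miss it whatever the true effect. In a non-inferiority trial the second error matters as much as the first, because a non-significant difference in a small subsite may be taken as evidence that retention is safe there.

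**The label.** An analysis named in the protocol before the first patient is pre-specified. If it is called post-hoc, readers cannot tell it from analyses added after the results are known, and the label leaves the form of the depth variable open. Depth is a factor readers will look at, since the Eligibility criteria section keeps in the trial patients whose tumours prove to be T3 after surgery because of deep infiltration.

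**Working it through.** The point disputes no figure in the plan. The inputs taken from the Sample size section are 3-year OS of 78% (retention) and 80% (dissection), with 261 and 260 patients. The number of levels comes from the Stratification section.

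**1. Expected deaths at 3 years**, no dropout applied:
261 × 0.22 + 260 × 0.20 = 57.4 + 52.0 = 109.4, about 109.

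**2. Number of level-by-level comparisons:**
2 T stages + 6 subsites = 8 per endpoint.

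**3. Chance of at least one nominal p<0.05 with no true effect, per endpoint**

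| Approach | Result |
|---|---|
| 8 tests treated as independent: 1 − 0.95^8 | 34% |
| Simulation, Cox Wald test in each level | 22–23%; 20–27% under other subsite mixes |
| Simulation, log-rank test in each level | 32%; 29–32% under other subsite mixes |
| Simulation, deaths compared as proportions | 32% |
| Two interaction tests, one per factor: 1 − 0.95^2 | 9.75% |

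The Cox and log-rank simulations used 522 patients, 79% 3-year survival in both arms and assumed subsite shares of 45/20/10/10/8/7%. The comparison of proportions used 521 patients, 21% deaths, T1:T2 at 50:50 and shares of 45/20/10/15/5/5%. The Wald figures are lower because that test is conservative in very small subsites. The 9.75% assumes that the two tests are independent and hold their nominal level. The subsite test has 6 − 1 = 5 degrees of freedom on sparse data, so this is approximate.

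**4. Precision within levels.** With 1:1 allocation, SE(log HR) ≈ 2/√d for d deaths, and the 95% interval multiplies and divides the hazard ratio by exp(1.96 × SE).

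- Half of the patients: d ≈ 54.7, SE = 0.270, factor 1.70.
- One sixth of the patients: d ≈ 18.2, SE = 0.468, factor 2.5.
- A subsite with an assumed 7% share: d ≈ 109.4 × 0.07 = 7.7, about 8; SE = 2/√8 = 0.71, factor about 4.

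**5. Power of an interaction test, two equal halves.**
SE = √(4/54.7 + 4/54.7) = 0.382. The ratio of hazard ratios detectable with 80% power is exp((1.96 + 0.84) × 0.382) ≈ 2.9.

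**6. Why the form of depth should be fixed in advance.** In 3,000 simulated trials with no true effect, comparing deaths as proportions, an interaction test at one fixed cut-point was falsely positive in 5.0%. Taking the best of 13 cut-points (20th to 80th percentile in 5-point steps) raised this to 25.5%. The grid is an assumption. It shows the size of the risk, not what the plan says will be done.

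**7. The label, side by side.** The Others paragraph calls the histological analysis post-hoc and names depth. The Stratification section already lists depth as affecting OS. The Trial status section places the document before enrolment. These three statements do not fit together.

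**The case against.** Interaction tests, multiplicity rules and cut-points are commonly left to a statistical analysis plan, and none is shown here. That stands for anything merely absent. It does not cover what the article states: it names univariate Cox in subgroups, and it uses the word post-hoc for an announced analysis. A later plan would have to correct both statements, not just add detail.

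It can also be said that the post-hoc label errs on the side of caution, since it marks results as exploratory; that univariate Cox models in subgroups already give hazard ratios with intervals; that no subgroup claim is planned; and that the stated aim concerns T1–T2 N0 disease as a whole. All of this is fair. It is why the point is minor and why a family-wise error rate is only an illustration here.

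Four stronger readings are tempting, and the documents support none of them.

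- *That T stage and subsite are labelled post-hoc.* They are not. The label covers only the histological factors.
- *That univariate Cox is the stated method for the histological subgroups.* It is stated only for the stratification factors.
- *That depth cut-points will be chosen after the data are seen.* No sentence says so; the label only leaves this possible.
- *That the limitations paragraph of the Discussion commits to a survival subgroup by depth.* It does say "we will put the depth of invasion into the final analysis", but the purpose it gives is to clarify how depth relates to occult metastasis. It is not evidence of a planned treatment-effect subgroup for survival.

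**Conclusion.** The point holds as a minor correction to secondary analyses. The subgroup method stated for T stage and subsite does not answer whether the effect of retention varies between levels. Read level by level, it has a roughly 20 to 34% chance per endpoint of producing at least one nominally significant level when nothing is there, against about 10% for two interaction tests. If Cox Wald p-values are used, the lower part of that range (20–27%) applies. The range rests on the protocol's survival assumptions, no dropout, and subsite and T-stage mixes that the documents do not give. That the models would be fitted separately and read by their p-values is a fair reading of the abstract, not its wording.

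The post-hoc label for depth of invasion is wrong as written. A reader might infer that chance subgroup findings will drive the trial's conclusion. Nothing says so, and the primary comparison is a log-rank test of the whole groups, which this point does not touch.

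**What to change.** 1. For T stage and primary subsite, report the hazard ratio with its confidence interval in each level. Judge heterogeneity by one treatment-by-factor interaction per factor, in a Cox model on all patients, for OS and for PFS. State that no claim will be drawn from within-subgroup p-values. Put this in the Statistical methods section, which does not carry the abstract's Cox sentence.
2. Rename the depth-of-invasion analysis a pre-specified exploratory subgroup. Set its form before the data are seen, either continuous or with fixed cut-points, and test it by interaction in the same way.
3. Keep the term post-hoc for analyses added later.

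The cost is a few lines of text and one extra model per factor for each endpoint, with no extra patients or data. The drawback is low power: even for two equal halves, a ratio of hazard ratios of about 2.9 is needed for 80% power. A non-significant interaction should therefore not be reported as proof of a uniform effect, and the intervals should carry the message.

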### Statistical methods

#### Overall survival

This trial will be terminated when the last patient has been followed-up for 3 years. After the trial ends, the primary endpoints will be tested by means of two-sided log-rank tests.

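### Depth of invasion is named as prognostic but used for survival only in post-hoc subgroups; a pre-specified adjusted comparison would give a modest, nearly free gain in precision

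*Protocol article*

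**What the plan says.** - **Stratification.** The protocol article lists factors that can affect OS: T stage, primary subsite (ending "or hard palate), and depth of invasion [25"]). Depth is the third factor. Randomisation is then stratified on T stage and primary subsite only.
- **Statistical methods, Overall survival.** After the trial ends, "the primary endpoints will be tested by means of two-sided log-rank tests". No covariates or strata are named.
- **Statistical methods, Progression-free survival.** "We will use a two-sided log-rank test to check the difference in PFS between the two groups". Again no covariates or strata are named.
- **Abstract, Methods.** The only Cox analysis described is univariate, within subgroups defined by the stratification factors. Depth is not one of those factors.
- **Statistical methods, Others.** Depth enters survival through "post-hoc subgroup analyses on the basis of histological factors that were known to have effects on survival, such as depth of invasion".
- **Discussion, limitations.** "we will put the depth of invasion into the final analysis", with the stated purpose of clarifying how depth relates to occult metastasis.
- **Eligibility criteria.** Some clinical T1–T2 tumours will prove to be T3 after surgery because of deep infiltration. These patients stay in the trial.

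**The concern.** The protocol gives a factor that it regards as prognostic a role that does not suit it. A subgroup analysis asks whether the treatment effect differs by depth. It does nothing for the precision of the overall comparison between arms. The post-hoc label does not fit an analysis named before enrolment, and it leaves cut-points and model to be chosen once results are known.

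Depth is a sound covariate. It is a property of the tumour that predates randomisation, and the handling of level IIb cannot change it.

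Precision matters here. The Sample size section concedes that the 12% margin looks large and says that it was chosen to keep the sample size within reach. A narrower interval at no extra recruitment serves that constraint directly.

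**Working it through.** **Inputs from the Sample size section.** Retention: "we assumed the 3-year OS rate in the IIb retention group will be about 78"%. Dissection: "that in the IIb dissection group will be 80"%. Margin 12 points, power 80%, 261 and 260 patients. The prognostic strength of depth is not given. I assume hazard ratios of 1.5, 2.0 and 2.5 per SD of depth.

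**1. The plan's own figure.** The true difference is 2 points, so the distance to the margin is 0.12 − 0.02 = 0.10.
n per arm = (z₁₋α + z₀.₈)² × (0.80×0.20 + 0.78×0.22) / 0.10²
- One-sided 0.025: (1.960 + 0.842)² × 0.3316 / 0.01 = 260.3, so 261. This matches the plan.
- One-sided 0.05, as labelled: 205.0, so 206. This does not match. It is a separate matter; I use 0.025 below because it reproduces the stated size.

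**2. Unadjusted precision.**
Variance = 0.16/260 + 0.1716/261 = 0.001273; SE = 3.57 points; 95% half-width = 1.96 × 3.57 = 7.0 points.

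**3. How much of that variance is chance imbalance in depth, ignoring stratification.**
- SD of the between-arm difference in mean depth = √(1/261 + 1/260) = 0.0876 SD.
- Slope of 3-year OS per SD of depth ≈ S × H × ln(HR), with S = 0.79 and H = −ln 0.79 = 0.236.
- Contribution = slope × 0.0876. Share of variance = contribution² / 0.001273.

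| HR per SD | Slope | Contribution (points) | Share of variance | Simulated reduction (two runs) |
|---|---|---|---|---|
| 1.5 | 0.076 | 0.66 | 3.4% | 3.6%, 4.0% |
| 2.0 | 0.129 | 1.13 | 10.0% | 8.6%, 9.5% |
| 2.5 | 0.171 | 1.50 | 17.6% | 16.8%, 14.7% |

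The simulations used 1,500 and 6,000 trials per setting. The hand calculation and both runs agree on roughly 4%, 9% and 15–17%. These are upper bounds, because T stage is treated as carrying no information on depth.

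**4. Allowing for T-stage stratification.** Simulating T-stage-stratified randomisation with depth partly carried by T stage gives reductions of about 2–3%, 4–7% and 8–12%. As a plausibility check, suppose that T stage explains a quarter to a half of the variance of depth (assumed). Multiplying the shares in step 3 by 0.75 and 0.5 gives 1.7–2.6%, 5.0–7.5% and 8.8–13.2%, which is close.

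**5. What 2–12% buys.** Half-width = 7.0 × √(1 − r). Power = Φ(0.10/(0.0357√(1 − r)) − 1.96). Equivalent extra patients = 521/(1 − r) − 521.

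| Reduction r | Half-width (points) | Power | Equivalent extra patients |
|---|---|---|---|
| 0 | 7.0 | 80.0% | – |
| 2% | 6.9 | 80.8% | 11 |
| 7% | 6.7 | 82.8% | 39 |
| 12% | 6.6 | 84.8% | 71 |

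The 7.0 comes from a formula that takes no credit for stratification, so this step is approximate.

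**6. Validity of the unadjusted test.** Non-inferiority tests on the hazard-ratio scale were simulated with a binary deep-invasion covariate, hazard ratio 1.5–3.0 and prevalence 30% or 50% (all assumed). One-sided type I error was 1.9–2.9% unadjusted and 2.1–2.9% adjusted, against a nominal 2.5%. The unadjusted log hazard ratio showed no material bias. Adjustment changed power by −1 to +2 points at hazard ratios of 1.5–2 and by +4 to +6 points at 3 (Monte Carlo SE about 1.2 points).

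**The case against.** **An unadjusted comparison is no error in a randomised trial.** This stands. A reader might infer that leaving depth to chance biases the OS comparison. The documents do not support that: randomisation balances depth in expectation, and step 6 shows no inflation of type I error. At a hazard ratio of 2.0, an imbalance at the 95% chance limit (1.96 × 0.0876 = 0.17 SD) shifts the OS difference by about 2 points (0.17 × 0.129 = 2.2). That shift is one component of the 7.0-point half-width and not an addition to it.

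**The gain is small and rests on assumed hazard ratios.** This stands too. T stage is stratified and tied to depth, so depth is not left wholly to chance, and 4–17% can be read only as an upper bound.

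**Covariate lists belong in the statistical analysis plan, which is not shown.** This stands in part. The unseen plan may contain an adjusted analysis, so one cannot say that none exists. But the article does more than stay silent: it assigns depth a role in the survival analysis and labels that role post-hoc. The Discussion sentence does not repair this, because its stated purpose is occult metastasis.

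**Depth is measured after randomisation, and its source is inferred.** No section says outright that depth is read from the specimen. This follows from the word histological and from the account of T3 confirmed after surgery. Surgeons know the allocation, and the article does not describe blinding of the pathologist. That calls for a safeguard but does not rule out adjustment.

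**Conclusion.** The point holds as an inexpensive improvement to the analysis. It does not show that the planned comparison is invalid. The article names depth as prognostic, tests OS and PFS without covariates, and uses depth for survival only in subgroups that it calls post-hoc. This forgoes about 2–12% of the variance of the 3-year OS difference, or roughly 1 to 5 points of power from 80%.

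The size rests on assumed hazard ratios of 1.5–2.5 per SD, on T stage carrying part of the information in depth, and on depth being available for nearly all patients. A weaker effect of depth, or a closer link with T stage, would shrink the gain further.

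**What to change.** - **Overall survival and Progression-free survival sections.** Before outcome data are seen, pre-specify comparisons adjusted for depth of invasion (continuous, in mm, no cut-point) together with T stage and subsite. Use a Cox model for the hazard ratio. For OS, add a standardised 3-year difference with its confidence interval, set against the 12-point margin. Report the unadjusted result alongside.
- **Missing depth.** State in advance a simple rule that keeps every randomised patient in the analysis. Assigning the mean depth for the patient's clinical T stage is one option.
- **Source of depth.** Take it from the routine pathology report, since it is read after randomisation in a trial where surgeons know the allocation.
- **Others section and Abstract.** Drop the post-hoc label for an analysis named in advance.
- **Discussion.** Say what putting depth into the final analysis means, and align it with the above.

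The cost is about a paragraph of analysis wording. If depth is already in the pathology report, as the text implies, no new visits, patients or measurements are needed. The article states that enrolment had not started, so the change can be made cleanly. The interval set against the margin would itself be an addition, because the article describes only a log-rank test.
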